### Study design

The study has a stepped-wedge design [57], meaning a prospective study with concurrent controls that later cross over to intervention (Fig. 1). Study sites are enrolled in matched pairs. Within each pair, one facility is randomly assigned to “immediate intervention” status and receives the intervention as early as possible during the project period, following baseline data collection. The research team provides coaching to co-facilitators and champions throughout the implementation process, in order to enhance fidelity, engagement, and effectiveness. The other facility, designated as the “lagged intervention” site, has status-quo control group status for the first half of the project, continuing with the safety process already in place at that facility until mid-way through the timeline. At that point, the three immediate intervention sites will continue with the HWPP process independently, and the HWPP coaching will be transferred to the lagged intervention sites.

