#### Effectiveness evaluation

The pre/post “mini-surveys” will be analyzed to assess short-term effectiveness of locally-designed interventions within the proportion of the workforce expected to benefit. Employee participation in DT-promoted activities will be compared between study groups and over time (pre- vs post-intervention).

Organizational-level improvements in worker engagement, communication or shared understanding between management and workforce, SC authorization of resources, or uptake and institutionalization of new practices will be interpreted as effectiveness of the participatory intervention process, at the overall study level.

Assuming that both groups intervene on similar topics over time, pooled effectiveness analyses will compare AES data in the immediate intervention and lagged intervention groups. If sufficient numbers of workers complete more than two surveys, we will also use a difference-in-difference approach. Reporting of individual-level outcomes (e.g., changes in occupational exposures, health beliefs and behaviors) will follow the CONSORT guidelines for cluster randomized trials [64].

Statistical power calculations for intention-to-treat comparisons of several key outcomes (Table 2) were conducted for difference-in-difference analysis, with two-sample differences at the population level. The facilities within each pair are of different workforce sizes, so we assumed conservatively the smaller of the facilities from each pair in both groups. Full-time equivalent denominators were assumed to represent 90% of headcount; a 75% response rate gave samples of about 1650 workers per group. We used a binomial distribution for proportions (e.g., smoking) and Gaussian distribution for means (e.g., body mass index (BMI)). Starting values were taken as those found in our prior healthcare study using a similar instrument [31, 32, 65]. Modest differences should be readily detectable, assuming facility-wide implementation of each HWPP intervention.

**Table 2 Tab2:** Smallest detectable differences in selected outcomes with 80% power (alpha = 0.05, two-sided *p*-value)

Outcome	Baseline value	Detectable difference
Injury rate	0.71 / FTE	.062 / FTE
Smoking	Prevalence 25.6%	6.0%
BMI	Z = 28, SD = 9	0.9
Health self-efficacy	Z = 27, SD = 8.5	0.8
Work ability	Z = 8.9, SD = 2	0.19

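### Table 2 takes about 1650 workers per group as independent although facilities are randomised, so the printed detectable differences do not carry 80% power

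*Protocol article*

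**What the plan says.** Under Study design, the protocol article states that "Study sites are enrolled in matched pairs" and that one facility of each pair is allocated at random to immediate intervention. Setting and population gives six facilities in three pairs. Methodologic considerations says that the intervention is given to the whole facility and that resources did not allow enough sites. Study revisions after the start date reports that one facility has since withdrawn, which leaves five facilities and two intact pairs.

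Under Data analysis, Effectiveness evaluation, the power calculations "were conducted for difference-in-difference analysis, with two-sample differences at the population level". On sample size, "we assumed conservatively the smaller of the facilities from each pair in both groups", "Full-time equivalent denominators were assumed to represent 90% of headcount", and "a 75% response rate gave samples of about 1650 workers per group". Proportions are treated as binomial and means as Gaussian. Table 2 then lists the smallest detectable differences "with 80% power (alpha = 0.05, two-sided": injury .062 per FTE, smoking 6.0%, BMI 0.9, health self-efficacy 0.8 and work ability 0.19. The paragraph ends: "Modest differences should be readily detectable, assuming facility-wide implementation of each HWPP intervention". The same section says that reporting of individual-level outcomes "will follow the CONSORT guidelines for cluster randomized trials".

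**The concern.** When whole facilities are allocated, workers in one facility share management, staffing, case mix and local events. Their outcomes, and their changes over time, are therefore correlated. The variance of a group comparison then depends mainly on how facilities vary and how many there are, and much less on the number of workers. A calculation that counts workers as independent gives detectable differences that are too small. The number of facilities also limits the degrees of freedom.

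At stake is the only power statement in the article. A reader would take it that a 0.9-unit BMI change or a 6-point smoking change would be found four times in five. A null result would then be over-read as evidence of no effect.

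**Working it through.** **Inputs from the article.** Two-sided alpha 0.05 and power 80%, so K = 1.960 + 0.842 = 2.802; n = 1650 per group; SDs of 9 (BMI), 8.5 (self-efficacy) and 2 (work ability); baseline values of 0.256 (smoking) and 0.71 (injury); six facilities, three per group.

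**Assumptions.** Equal facilities, m = 1650/3 = 550 respondents each. ICC and cluster autocorrelation (CAC) are not given, so ranges are used.

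**Step 1: reproduce Table 2 with independent workers (design effect 1).**

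| Row | Formula | Result | Printed |
|---|---|---|---|
| BMI | 2.802 × 9 × √(2/1650) | 0.878 | 0.9 |
| Self-efficacy | 2.802 × 8.5 × √(2/1650) | 0.829 | 0.8 |
| Work ability | 2.802 × 2 × √(2/1650) | 0.195 | 0.19 |
| Smoking | 2.802 × √(4 × 0.256 × 0.744/1650) | 6.02% | 6.0% |
| Injury | 2.802 × √(4 × 0.71 × 0.29/1650) | 0.0626 | .062 |

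All five rows match to rounding or truncation. The mean rows use a plain two-sample variance. The smoking and injury rows use a difference-in-difference variance with four independent samples; a plain two-sample binomial would give about 4.3 points for smoking and about 0.044 for injury. The table therefore mixes two variance conventions. The mean rows equal a difference-in-difference only if the within-worker correlation is about 0.5, which is not stated.

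**Step 2: difference-in-difference, six facilities.** For two cross-sections, the variance is multiplied by 1 + (m − 1)ICC − m × ICC × CAC. Detectable differences grow by the square root of this. For 80% power with t on 4 degrees of freedom, K is replaced by 3.761, a further factor of 3.761/2.802 = 1.34.
- All facility variance cancels (CAC = 1): variance factor about 1; inflation 1.00 (normal) or 1.34 (t, 4 df). In the t case, power at the printed differences is about 54–58%.
- ICC 0.01, CAC 0.8: 1 + 5.49 − 4.40 = 2.09; √2.09 = 1.45 (normal); 1.45 × 1.34 = 1.94 (t, 4 df). Power at the printed differences is about 46–51% (normal) or 30–33% (t). The BMI difference becomes 1.27 or 1.70.

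**Step 3: cross-sectional group comparison, six facilities.** The design effect is 1 + 549 × ICC.
- ICC 0.001: 1.55, inflation 1.24 (normal).
- ICC 0.005: 3.75, inflation 1.94.
- ICC 0.01: 6.49, inflation 2.55.

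**Step 4: five facilities (3 v 2, 550 each).** The standard error grows by √[(1/3 + 1/2)/(2/3)] = 1.118. With 3 df, K becomes 4.256, a factor of 1.519.
- No remaining facility variance: 1.118 × 1.519 = 1.70.
- ICC 0.01, CAC 0.8: 1.70 × 1.45 = 2.46.

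**Step 5: randomisation floor.** Two intact pairs allow 2² = 4 allocations. A paired randomisation test cannot give a two-sided p below 2/4 = 0.5. With the original three pairs the floor was 2/8 = 0.25.

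**The case against.** The best defence is that power was stated for difference-in-difference, in which stable facility differences cancel, and that pairing can recover more. This stands as a limit on size. It means that the larger cross-sectional figures, such as a factor of 2.55 at ICC 0.01, should not be read as the loss for the planned contrast. It does not rescue the table. Differencing leaves facility-by-period variation in place, and the few degrees of freedom remain. The article also makes the difference-in-difference analysis conditional on enough workers completing more than two surveys; otherwise it describes a pooled comparison of groups.

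A second defence is that smoking and injury carry an extra √2 that could be a clustering allowance. Taken alone, those rows would fit a design effect of 2. The four-sample variance explains them equally well, and the mean rows leave no room for any allowance.

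A third is that the article calls its assumption conservative. That word covers only the use of the smaller facility of each pair.

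A reader might go further and infer that the trial will test worker-level data naively, with a grossly inflated type I error. The article does not support this: it specifies no such test, it commits to cluster reporting, and the model may properly stand in an analysis plan that is not shown. Nor can one infer that the trial's primary aims lack power. The registered primary outcomes are attendance, engagement, committee activity and scope of issues, none of which is in Table 2. The p-value floor binds only if a randomisation test is used, and the article does not specify one.

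**Conclusion.** The point holds for Table 2 and for the sentence on ready detectability, whatever analysis model is adopted later. The printed differences have 80% power only if workers are independent within facilities and inference ignores the number of facilities.

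Any facility variance that baseline differencing does not remove enlarges every row, and facility-level inference on 4 df adds a factor of 1.34 by itself. Beyond that, size rests on assumed ICC and CAC values, equal facilities of 550 and two cross-sections. A reasonable summary for six facilities is 1.34 to 1.94 under difference-in-difference with t on 4 df, and 1.24 to 2.55 (normal) for a cross-sectional comparison at ICCs of 0.001 to 0.01. Five facilities do worse. The error concerns the longer-term effectiveness outcomes, not the registered primary process outcomes.

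**What to change.** - Recompute Table 2 for the facilities that remain, over a stated range of facility-by-period ICCs taken from the prior healthcare study or the baseline All-Employee Survey. Take degrees of freedom from the number of facilities.
- Use one stated variance convention for all rows, and give the within-worker correlation if the mean rows rely on it.
- Withdraw the claim that modest differences are readily detectable.
- Base the survey group comparison on an analysis that accounts for facility with a small-sample correction.

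The cost is a recalculation, revised wording and less favourable stated figures. If the analysis plan does not already account for facility, the last item is also a change to the analysis. The sites, the intervention and the primary outcomes stay as they are. Whether to give up testing at the 0.05 level in favour of estimates with intervals is a separate choice that this correction does not require.

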## Background and rationale

### Occupational health and safety in the healthcare sector

Healthcare is one of the largest sectors in the U.S. economy, with over 16 million employees, representing 11% of the U.S. labor force [1]. Eighteen of the 30 fastest-growing professions in the U.S. are in healthcare and associated sectors; they are expected to create more than 3.4 million additional jobs by the year 2028 [2]. The largest projected increases are for home health professionals and personal care assistants [2, 3]. Other professions such as nurse practitioners, physician technicians, and medical assistants also represent steady demand as the healthcare sector shifts towards team-based services [3].

Numerous exposures in the healthcare work environment include excessive physical workload (e.g., patient handling), biological agents, cleaning and disinfection chemicals, shiftwork with extended hours, electronic data entry, assaults, and psychosocial stressors. Not all of the resulting health effects are recognized or reported as work-related. Nationally, the reported incidence rate of recordable non-fatal occupational injuries and illnesses for healthcare and social assistance jobs was 4.1 per 100 full-time workers in 2017 and 3.9 in 2018 [4].

The type and severity of injuries vary by job title. Compared to all occupations (private sector), psychiatric aides have among the highest incidence rates for non-fatal workplace injuries requiring days away from work (647.7 per 10,000 full time workers) [5]. Among other healthcare professions, orderlies and nursing assistants’ rates were 283.3 and 255.7, respectively [5]. Rates for registered nurses (RNs) were 88.4, licensed practical and vocational nurses (LPNs) 85.6, healthcare social workers 25.4, and mental health and substance abuse social workers 14.7 [5].

In 2018, incidence rates for nonfatal occupational injuries and illnesses resulting in days away from work among public sector (state government) healthcare occupations were considerably higher than those of their private sector counterparts [6]. Public sector psychiatric aides’ incidence rates were 1475.7 per 10,000 full time workers, nursing assistants 445.9, RNs 194.5, and LPNs 427.7 per 10,000 [7].

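### The injury-rate row of Table 2 matches a calculation that treats 0.71 injuries per FTE as a 71% proportion; on one FTE-year per person per period a count model gives a larger detectable difference.

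*Protocol article*

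**What the plan says.** The power statement is in the protocol article under Data analysis, Effectiveness evaluation, with results in Table 2. The calculations "were conducted for difference-in-difference analysis, with two-sample differences at the population level", and the table is headed as the smallest detectable differences "with 80% power (alpha = 0.05, two-sided" p-value. On sample size, the section says "we assumed conservatively the smaller of the facilities from each pair in both groups", and then: "Full-time equivalent denominators were assumed to represent 90% of headcount"; "a 75% response rate gave samples of about 1650 workers per group".

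On distributions the section says only "We used a binomial distribution for proportions (e.g., smoking) and Gaussian distribution for means".

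Table 2 gives the injury outcome as a rate: baseline 0.71 / FTE, detectable difference .062 / FTE, with no SD. Smoking is a prevalence of 25.6% with detectable difference 6.0%. The other three rows are means with an SD. For the injury row the article gives no count distribution, follow-up time or allowance for repeat injuries, and does not say whether injuries are self-reported or come from claims.

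**The concern.** An injury rate per FTE is a number of events divided by person-time. One worker can be injured more than once, and the rate can exceed 1. Its sampling variance is therefore not p(1-p). With a Poisson count the variance per FTE-year equals the rate, 0.71, and overdispersion raises it. The binomial variance at 0.71 is 0.71 x 0.29 = 0.206, smaller by a factor of 3.4. With only a binomial and a Gaussian distribution named, and no SD in the row, it was natural to ask whether 0.71 had been entered as a proportion.

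If so, the stated detectable difference is too favourable. Injury is the first outcome listed in Table 2, and the section concludes from that table that modest differences will be easy to detect.

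**Working it through.** **Inputs.** All come from Data analysis, Effectiveness evaluation and Table 2: baseline 0.71 per FTE; stated detectable difference .062 per FTE; 80% power, two-sided alpha 0.05, so z sum k = 1.9600 + 0.8416 = 2.8016; n about 1650 per group, equal groups; difference-in-difference (DiD). The text allows two readings of FTE. If 1650 is 75% of headcount, headcount is 1650/0.75 = 2200 and FTE is 0.9 x 2200 = 1980. If 1650 is 75% of FTE, FTE is 2200. I use 1650, 1980 and 2200. One FTE-year per person per period is my assumption, as the article gives none.

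**Step 1: reproduce the stated figure.** Binomial DiD, four independent cells: d = k x sqrt(4p(1-p)/n).

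- Injury: 2.8016 x sqrt(4 x 0.71 x 0.29/1650) = 0.0626, stated .062. Letting one cell take the shifted proportion gives 0.0615 to 0.0634. The n implied by .062 is 1682, within 2% of 1650.
- Smoking, same formula: 2.8016 x sqrt(4 x 0.256 x 0.744/1650) = 0.0602, stated 6.0%.
- A two-sample binomial, k x sqrt(2p(1-p)/n), gives 0.044 and 0.043 and fits neither row.

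Both rows without an SD thus come from one binomial DiD formula at the stated n and design.

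**Step 2: use a count variance.** Poisson DiD: d = k x sqrt(4 x 0.71/F). Poisson two-sample: d = k x sqrt(2 x 0.71/F). F is FTE-years per group (per period for DiD). Power at .062 is Phi(0.062/SE - 1.96), with SE the square-root term.

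| F | DiD d | ratio to .062 | power at .062 | two-sample d | ratio to .062 | power at .062 |
|---|---|---|---|---|---|---|
| 1650 | 0.116 | 1.87 | 32% | 0.082 | 1.33 | 56% |
| 1980 | 0.106 | 1.71 | 37% | 0.075 | 1.21 | 64% |
| 2200 | 0.101 | 1.62 | 41% | 0.071 | 1.15 | 68% |

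**Step 3: how much person-time would rescue .062?** Solve for F: k^2 x 4 x 0.71/0.062^2 = 5,799 FTE-years per group per period for DiD, and k^2 x 2 x 0.71/0.062^2 = 2,899 per group for two-sample. If one cell's variance is taken at the reduced rate, these become 5,672 and 2,773. Divided by 1650 to 2200 FTE, they correspond to about 2.6 to 3.5 years per worker in each period (DiD), or about 1.3 to 1.8 years (two-sample).

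**Step 4: check which design the other rows use.** The three Gaussian rows fit the two-sample formula k x SD x sqrt(2/n): 0.88, 0.83 and 0.195, against stated 0.9, 0.8 and 0.19. DiD would give 1.24, 1.17 and 0.276. This is why both designs are carried in Step 2.

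**The case against.** The strongest objection is that the binomial match is an inference. The article never says that injury was treated as a proportion, and a count calculation can reach the same number. Poisson with 1980 FTE over 1.5 years (2,970 FTE-years) gives 0.0613 two-sample, and over 3 years per period (5,940) gives 0.0613 DiD. Both are about as close to .062 as 0.0626 is. Administrative files are collected annually, retrospectively and prospectively (Evaluation, Formative evaluation), so more than one year per period is plausible. This stands to the extent that one cannot say the row arises only from a binomial formula. It does not support the row as written. The person-time is unstated, the two-sample route drops the design the section says was used, and the DiD route needs about 3 years in each period. The binomial match needs no input beyond those given.

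It is also fair that the size of the error depends on the design and person-time, so no single multiplier is established. Both ranges are therefore reported.

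Three stronger readings are tempting, and the article does not support them.

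- A reader might infer that 0.71 is itself wrong. The Background says the national recordable rate "was 4.1 per 100 full-time workers in 2017 and 3.9 in 2018", and for public sector psychiatric aides "incidence rates were 1475.7 per 10,000 full time workers". But those are recordable or days-away injuries. The starting values in Table 2 came from a prior survey with a similar instrument, and the All-Employee Survey covers injury. Self-reported injury can be far more frequent, so the gap shows no error, only that the source should be named.
- A reader might infer that the trial will analyse injury as a proportion. Nothing says so: Table 2 labels the outcome a rate, and the text after it speaks of claim rates.
- A reader might infer that the row undermines the trial's main inference. The registered primary outcomes are attendance, engagement, committee activity and scope of issues (Evaluation, Process evaluation), and the number of sites was limited by resources (Methodologic considerations), not set by Table 2.

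**Conclusion.** The point holds as a should-fix correction of a stated power figure. On the inputs given, the injury row is evidently a binomial DiD calculation with p = 0.71, which understates the variance of an event rate per FTE. With Poisson variance and one FTE-year per person per period, the detectable difference is about 0.10 to 0.12 per FTE under the stated DiD design, with power at .062 of about 32 to 41% in place of 80%. Under a simple two-sample comparison it is 0.071 to 0.082, with power of 56 to 68%.

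These figures rest on 1650 to 2200 FTE, independent cells and no overdispersion. Longer person-time would shrink them; repeat injuries concentrated in some workers, or clustering by facility, would enlarge them. If 0.71 is in truth the proportion of workers with any injury, the arithmetic is right to rounding and the label is wrong.

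**What to change.** Recompute and restate the injury row as a count rate, Poisson or negative binomial, giving the FTE person-time assumed per group and period and the design used (DiD or two-sample). State whether 0.71 is self-reported injury or claims. If it is the proportion of workers injured, relabel the row as a proportion and remove the FTE unit. Then check whether the closing statement on detectability still holds for injury.

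The cost is one recalculation and a few words in Table 2 and its text. Enrolment, data collection and the registered primary outcomes do not change. Unless longer person-time was assumed, the restated figure will be less favourable.

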#### Cost-effectiveness evaluation

We will estimate cost-benefit for each intervention and cost-effectiveness (cost-outcome) for selected outcomes. Cost will be represented by organizational inputs (equipment, personnel effort) and benefits in terms of adverse outcomes avoided (e.g., worker injury prevented, dollars of WC claims avoided, unit of body weight lost, resident fall prevented).

The primary challenges to cost-benefit analyses lie in the measurement of costs of intervention and in assigning a monetary value to the outcomes. Data from the control group will be used to estimate the cost (lost workdays, turnover, training, hiring substitutes) of not intervening. The analyses will calculate “net present value,” or the sum of all costs and benefits associated with the intervention, measured at a specific time point by discounting each cost and benefit by the opportunity cost of capital [66]. This sum is positive when an intervention provides a benefit greater than its costs. Some intervention costs involve large initial outlays and others recur over time, such as the costs of equipment maintenance and employee training. Benefits may or may not be immediately visible or may also increase over time. This method allows adjustment for the difference in timing of each monetary value through the discounting of each amount by the opportunity cost. In other words, the benefits of interventions are incremental, estimated per year. This also implies that, in order to be cost-effective, the benefits of intervention need to be large enough to outweigh the opportunity cost of capital that could have alternative uses.

As noted above, for some interventions, changes in WC costs will be meaningful. Other interventions may affect health outcomes not generally attributed to working conditions, such as obesity or sleep quality and its sequelae. In this case, benefits would likely be severely underestimated by relying only on WC costs, and other metrics are needed. In either case, benefits may also include reduced worker fatigue, higher productivity, fewer employee errors, or improved patient care. To aid in understanding, some AES items address knowledge and use of the internal reporting system and WC; self-assessed work ability and productivity; perceived quality of patient care; and intention to leave the job. However, these benefits are difficult to assign a monetary value. We will work with the partnering facilities to attempt to develop conservative estimation algorithms, using survey measures and administrative data.

An approach that does not require assigning dollar value to health or other non-monetary, measurable benefits (improved worker morale) is cost-effectiveness or cost-outcome analysis, which produces estimates of the cost to achieve a given unit of benefit, e.g., reducing body mass index by one point. The cost is estimated by recording the efforts and resources required to implement the program and applying dollar values to each one, as above. We will then estimate the investment relative to the program benefits achieved.

